##### Sample size calculation

The sample size was calculated using a comparison between group change in the HADS Depression subscale scores. With a 5% significance level and 90% power, we determined that 48 subjects per group will be required for the trial, in order to detect a standardized effect size Cohen’s *d* = 0.68, which is equivalent to a difference in HADS score at the end of the trial of around 2.4 points, assuming a standard deviation of 3.5 found in previous studies from our lab that used the same outcome. To account for up to 30% attrition, we plan to recruit a total of 140 participants into the study.

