##### Statistical analyses

We will follow the CONSORT guidelines for randomized controlled trials [49]. The statistical analysis of the data will be conducted by a statistician blinded to the treatment group. The primary outcomes will be the total HADS score and secondary analysis will be conducted using the Anxiety and Depression subscales. Intention to treat will be used for our primary analysis, where subjects will be analysed in the groups they were randomized regardless of compliance of having dropped out. The mixed effect model, where subjects are the random effects, time (baseline, 12 weeks and 36 weeks) and group (CaCBT and Standard CBT) as well as the interaction between time and group will be entered as fixed factors, with gender and baseline HADS as covariates. The significance of the interaction between group and time tests for difference in HADS score at 3 or 6 months and will be used to declare the intervention effective. Since recruitment will be conducted in 3 sites, these sites will also enter the model as random effects. We will also control for therapists variation by coding them as a variable in the dataset, then adding them to the model as a random effect. Mixed effect models estimated through maximum likelihood are able to account for dropouts under the assumption they are missing at random (MAR) [50, 51]. Comparison between dropouts and completers will be conducted at baseline to look at evidences of differences between them, and if significant differences are found, they will be accounted for by adding the variable as a control in the model. A significance level of 0.05 will be used to declare the CaCBT performs better than standard CBT. A diagnostic analysis will be conducted using Cook’s distance to detect possible influential data points, and if any is found, results without these subjects will be also presented if they lead to meaningfully different conclusions. Residuals will be checked for heterogeneity of variance that, if found, will be addressed by the use of robust “sandwich” type standard errors. We may also conduct a sensitivity analysis using completers only with ANCOVA and inverse propensity weighting, where weights are the estimate probability of dropping out estimated by a logistic regression model having baseline characteristics as predictors of the subjects. Such ANCOVA has the HADS score at the end of the trial as the outcome and HADS at baseline as the covariate, while also controlling for gender and sites. This approach is suggested in [52]. Finally, a similar ANCOVA without weights will be conducted using last observation carried forward (LOCF) and all subjects. If more than 10% of the subjects are found to be non-compliant, a per-protocol analysis will also be conducted where non-compliant subjects are removed. All these extra analyses will provide information on the robustness of the primary analysis through the mixed effect model.

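### Beyond the pre-set terms, further covariates enter the primary mixed model only if a significance test separates dropouts from completers, a poor criterion for supporting the missing-at-random assumption

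*Protocol article*

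**What the plan says.** Under Phase 2, Statistical analyses, the protocol article makes the maximum-likelihood mixed model primary. Time, group and their interaction are fixed factors, "with gender and baseline HADS as covariates". Subjects and therapists are random effects, and "these sites will also enter the model as random effects". These terms are unconditional. The section notes that such a model handles dropout if data are MAR.

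It then adds a conditional step, which starts with a screen: "Comparison between dropouts and completers will be conducted at baseline". The consequence of a positive screen is given in the same sentence of the protocol: "if significant differences are found, they will be accounted for by adding the variable as a control in the model". The only model described up to that point is the mixed model. The ANCOVA analyses come later and are described as supplementary: "All these extra analyses will provide information on the robustness of the primary analysis through the mixed effect model". The conditional step therefore applies to the primary model.

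The comparison is described without reference to treatment arm. A completers-only ANCOVA with inverse propensity weighting, whose dropout model uses baseline characteristics, is offered as something that may be done. An unweighted ANCOVA with last observation carried forward is also planned.

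Under Sample size calculation, 48 per group is raised to 140 in total: "To account for up to 30% attrition".

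**The concern.** A baseline variable helps the MAR argument if it is related both to dropout and to HADS, given what is already in the model. The planned rule looks at only half of that, and by p-value. A non-significant comparison does not show that a variable is unrelated to dropout, and a significant one says nothing about its relation to HADS.

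Pooling the arms adds a second weakness. In a randomised comparison, a dropout predictor left out of the model biases the group difference mainly when its link with dropout differs between arms. A pooled comparison can average such a pattern away.

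At stake is the model used to declare CaCBT effective. Part of its covariate set is unknown until dropout has occurred, and the variables most needed may be left out. The Background and Discussion expect fewer dropouts with CaCBT. A different rate does not prove a different mechanism, but it makes an arm-specific one plausible.

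**Working it through.** **1. The plan's own figure.** Inputs from Sample size calculation: d = 0.68, 5% significance, 90% power. Two-sided, n = 2(1.960 + 1.282)²/0.68² = 45.5, so 46 per group (47 by the t-test version), against 48 stated. Attrition: 96/0.70 = 137.1, so 138, against 140 stated. The sample size reproduces closely and is not in question.

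**2. Size of the screening comparison.** 0.30 × 140 = 42 dropouts; 140 − 42 = 98 completers. The screening level is not stated; 0.05 two-sided is assumed.

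The standard error of a standardised difference is √(1/42 + 1/98) = 0.184. The smallest observed difference reaching significance is 1.977 × 0.184 = 0.36 SD.

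Power of the two-sample t-test:

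| True difference (SD) | 42 vs 98 | 28 vs 112 (20% attrition, assumed) |
|---|---|---|
| 0.2 | 19% | 16% |
| 0.3 | 37% | 29% |
| 0.4 | 58% | 47% |
| 0.5 | 77% | 65% |

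**3. What the rule does to the treatment effect.** A simulation with no treatment effect, 8,000 runs per scenario. From the document: n = 140, 1:1 allocation, attrition about 30%, SD 3.5 to convert to HADS points. Assumed: one extra baseline covariate X, uncorrelated with baseline HADS; a correlation of 0.5 between X and the outcome; and the log-odds of dropout per SD of X shown below. The analysis is a single-time ANCOVA with baseline HADS always included, standing in for the three-time mixed model. X is added only if the pooled comparison gives p < 0.05 (the planned rule), or always.

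| Log-odds of dropout per SD of X (control, CaCBT) | X selected | Planned rule: bias, type I error | X always in: bias, type I error |
|---|---|---|---|
| 0, 0 | 5% | 0.00, 5% | 0.00, 5% |
| 0.5, 0.5 | 75% | 0.00, 5% | 0.00, 6% |
| 0, 0.7 | 41% | −0.21, 7% | 0.01, 5% |
| −0.4, 0.8 | 15% | −0.52, 14% | 0.00, 4% |
| −0.7, 0.7 | 5% | −0.68, 20% | −0.01, 5% |

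An independent rerun of the last scenario gave about −0.65 points and 19%. A rerun of the one-arm scenario gave about −0.2 points and 8%, with X selected in 43% of trials. Monte Carlo error on a type I error of 5% is √(0.05 × 0.95/8000) = 0.24 percentage points, so 7% is distinguishable from 5%. The sign of the bias follows from the assumed signs and would reverse with them.

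In the last row X is selected no more often than in the first, where it has nothing to do with dropout. The pooled screen cannot tell these two cases apart.

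**4. Scale.** Against the 2.4-point target difference, 0.21 points is 9% (0.21/2.4) and 0.65 points is 27% (0.65/2.4).

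**The case against.** The case for leaving the rule alone has real content.

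- **Most of the model is fixed.** A reader might infer that every covariate depends on the screen. It does not: gender, baseline HADS, site and therapist enter regardless, and baseline HADS is the baseline value of the outcome itself.
- **The rule is not outcome-driven.** A reader might infer freedom to choose a favourable model. The documents do not support that. The rule is written in advance, uses baseline data and dropout status only, and is applied by a statistician blinded to group. Type I error stayed at about 5% when dropout was unrelated to X or related to it equally in both arms.
- **Adding irrelevant variables by chance does little harm.** With 8 to 12 independent candidates (numbers assumed), the chance of adding at least one is 1 − 0.95⁸ = 34% to 1 − 0.95¹² = 46%. Each costs about a degree of freedom and does not bias a randomised comparison.
- **The larger bias is an adverse case.** It needs strong, opposite dependence by arm and a substantial link with outcome. The planned mixed model would also use 12-week scores from patients lost before week 36, which the single-time ANCOVA cannot do.
- **The list of candidates and the screening level may be in an analysis plan that is not shown.** Their absence is not criticised here.
- **No covariate list secures MAR.** Pre-specification only makes it more credible.

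All of these stand and limit the size of the point. They do not remove it. The rule itself is stated, so an analysis plan that carried it out faithfully would keep the weakness. The weighted ANCOVA, which has no stated significance screen, would help but is optional. Last observation carried forward makes no use of baseline predictors of dropout.

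**Conclusion.** The point holds for the additional covariates only. Choosing them by a dropout–completer significance test leaves part of the primary model unfixed and gives weaker support to MAR than a named list would.

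The firmest figure is the power of the screen: 37%, 58% and 77% for true differences of 0.3, 0.4 and 0.5 SD at 42 versus 98. It rests on the planned attrition and an assumed 0.05 level. The consequence for the treatment effect is conditional. Bias is nil when dropout depends on the variable equally in both arms, about 0.2 HADS points (type I error about 7%) with dependence in one arm only, and about 0.65 points (about 19%) with opposite dependence. These rest on the assumed correlation, log-odds and single-time ANCOVA, and on reading the comparison as pooled over arms.

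This is an inexpensive improvement that should be made. It is not evidence that the trial's type I error is generally inflated.

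**What to change.** In Statistical analyses, replace the conditional step with a short named list of baseline variables that are already collected and plausibly related to both dropout and HADS, for example age, WHODAS and BSI. Enter them in the primary mixed model alongside gender, baseline HADS, site and therapist, with a time interaction where needed, whatever the dropout–completer comparison shows. Keep that comparison as description, and show it by arm. Use any further variables it suggests only in a labelled sensitivity analysis, for example as auxiliary variables in multiple imputation, and state that analysis as planned rather than optional.

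The change is to wording only. The sample size does not move. The cost is a few degrees of freedom and the loss of the option to add covariates to the primary model later. If the chosen variables predict outcome there is some return: with the assumed correlation of 0.5 and dropout unrelated to X, the simulated SD of the estimated treatment effect was 0.51 points with X always included, against 0.62 under the planned rule.

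### The optional inverse-propensity sensitivity ANCOVA defines its weights as the probability of dropping out; neither that quantity nor its inverse restores the randomised population

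*Protocol article*

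**What the plan says.** All of this is in the Protocol article, Statistical analyses, unless another section is named.

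- The analysis is optional and restricted to completers: "We may also conduct a sensitivity analysis using completers only with ANCOVA and inverse propensity weighting".
- The same sentence gives the only definition of the weights: "weights are the estimate probability of dropping out estimated by a logistic regression model", with baseline characteristics as the predictors. The definition contains no inversion and no probability of completing. The approach is attributed to a cited reference that is not at hand.
- The weighted model is then described: "Such ANCOVA has the HADS score at the end of the trial as the outcome and HADS at baseline as the covariate", with gender and site also controlled for.
- The primary analysis is by intention to treat: "subjects will be analysed in the groups they were randomized regardless of compliance of having dropped out".
- The purpose of this and the other supplementary analyses is stated: "All these extra analyses will provide information on the robustness of the primary analysis through the mixed effect model".
- Sample size calculation gives the only figure for dropout: "To account for up to 30% attrition, we plan to recruit a total of 140 participants into the study".

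**The concern.** Inverse-probability weighting of completers has one job: to make those who were observed stand in for all who were randomised. It does so by giving extra weight to completers who resemble the people lost. The weight must therefore be the inverse of the probability of being observed. The article names the opposite probability, that of dropping out, and calls it the weight.

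An analyst who follows the sentence has two choices: use the probability as it stands, or invert it because the method's name says so. Neither leads to the right weight. At stake is a check on the missing-data assumption in a trial that plans for up to 30% attrition. A mis-weighted check may differ from the primary result, or agree with it, for reasons unrelated to whether that result is robust.

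**Working it through.** **Inputs from the article.** Attrition up to 30%, total 140, 1:1 allocation, difference 2.4 points, SD 3.5, d = 0.68, 48 per group.

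**The plan's own figure.** No number is given for the weights, so the only figure to reproduce is the sample size. With two-sided alpha 0.05 (sidedness assumed) and 90% power, the normal formula gives 2 × (1.960 + 1.282)² / 0.68² = 45.5, or 46 per group; the t-test version gives 47. The stated 48 per group has about 91% power. Inflating, 96 / 0.70 = 137.1, or 138 in two equal groups, against the stated 140. These figures hold up and do not bear on the point, except that they fix 30% as the planning value for dropout.

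**Algebra.** Let f(x) be the distribution of baseline characteristics among those randomised and p(x) the probability of dropping out. Completers are distributed as f(x)(1 − p(x)). After weighting by w(x) they represent f(x)(1 − p(x))w(x).

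- w = 1/(1 − p) gives f(x): the randomised population.
- w = p gives f(x)p(x)(1 − p(x)): neither the randomised population nor the dropouts.
- w = 1/p gives f(x)(1 − p(x))/p(x): tilted further towards those least likely to drop out, who are already over-represented.

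**Two-stratum illustration.** The stratum dropout rates and effects are assumptions; the article gives only the overall 30%. Take two equal strata with mean dropout 30%, and effects of 3.4 points (low dropout) and 1.4 points (high dropout), chosen so that the mean is 2.40.

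Share of the high-dropout stratum = (1 − p₂)w₂ / [(1 − p₁)w₁ + (1 − p₂)w₂]; target 0.500. Estimate = 3.4 − 2.0 × share.

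Worked for 15%/45%:

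- unweighted: 0.55 / (0.85 + 0.55) = 0.393, estimate 2.61
- w = p: 0.2475 / (0.1275 + 0.2475) = 0.660, estimate 2.08
- w = 1/p: 1.222 / (5.667 + 1.222) = 0.177, estimate 3.05
- w = 1/(1 − p): 0.500, estimate 2.40

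Over a range of assumed rates (share; estimate):

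| Dropout low/high | Unweighted | w = p | w = 1/p | w = 1/(1 − p) |
|---|---|---|---|---|
| 25%/35% | 0.464; 2.47 | 0.548; 2.30 | 0.382; 2.64 | 0.500; 2.40 |
| 20%/40% | 0.429; 2.54 | 0.600; 2.20 | 0.273; 2.85 | 0.500; 2.40 |
| 15%/45% | 0.393; 2.61 | 0.660; 2.08 | 0.177; 3.05 | 0.500; 2.40 |
| 10%/50% | 0.357; 2.69 | 0.735; 1.93 | 0.100; 3.20 | 0.500; 2.40 |
| 5%/55% | 0.321; 2.76 | 0.839; 1.72 | 0.041; 3.32 | 0.500; 2.40 |

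In every row both readings of the sentence are further from the target than no weighting. For w = p this is not an accident of the rates chosen. With equal strata at m ± d, w = p misses by more than no weighting when p₂(1 − p₂)² exceeds p₁(1 − p₁)². The difference between the two is 2d[(1 − m)(1 − 3m) + d²], which is positive for every d > 0 when m is below one third. At m = 0.30 it is 2d[0.07 + d²].

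**Simulation.** N = 140, 4,000 runs, 30% dropout depending on one standard-normal baseline covariate, logistic weights, completers' ANCOVA, mean effect 2.4, outcome SD 3.5. The slopes and the effect modifier are assumptions.

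| Setting | Quantity | Unweighted | w = p | w = 1/p | w = 1/(1 − p) |
|---|---|---|---|---|---|
| No effect modifier, logit slope 0.5 | SD | 0.62 | 0.65 | 0.69 | 0.63 |
| No effect modifier, logit slope 1.0 | SD | 0.62 | 0.73 | 0.85 | 0.65 |
| Modifier of 1 point per SD, slope 0.5 | Bias | +0.14 | −0.17 | +0.49 | +0.01 |
| Modifier of 1 point per SD, slope 1.0 | Bias | +0.25 | −0.29 | +0.95 | +0.01 |
| Modifier of 1 point per SD, slope 1.0 | RMSE | 0.67 | 0.78 | 1.31 | 0.65 |

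Without an effect modifier, all four schemes are essentially unbiased (within 0.02). What is lost is precision: at slope 1.0 the effective sample size is 98 unweighted, 70 with w = p, 51 with w = 1/p and 87 with the correct weight.

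**The case against.** The best defence is that the sentence names a standard method and cites a source for it. On that view the clause is loose wording: the logistic model estimates dropout, and the proper weight would be derived from it. That may well be what was intended, so the text should be read as a faulty description, not as evidence that a wrong estimator was deliberately chosen. But it does not make the sentence correct. The clause states which probability is the weight, nothing else in the article corrects it, and applying the method's name to that probability gives the worse of the two errors.

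The other objections limit how far the point reaches, and they stand.

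- A reader might infer that the trial's main conclusion is at risk. The article does not support that. Effectiveness is declared from the group-by-time interaction in the maximum-likelihood mixed model, which does not use these weights, and the weighted ANCOVA is only something that may be run.
- A reader might infer that the treatment effect will be biased. With dropout driven by baseline characteristics, as the weight model supposes, that requires those characteristics also to modify the effect. The article says nothing on this. The 2-point gap between strata in the illustration is large beside a 2.4-point planned effect.
- A reader might carry away a bias three times that of ignoring dropout. That ratio (0.65 against 0.21 at 15%/45%) belongs only to w = 1/p. For w = p it is 0.32 against 0.21, about 1.5 times.
- It has not been shown how often the check would falsely contradict or falsely support the primary result; no such rate was computed. In the simulation, the shift under w = p is smaller than the sampling SD of the estimate.

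**Conclusion.** The definition is wrong as written. Only 1/(1 − p) makes completers represent those randomised, and neither available reading of the sentence gives it. As specified, the analysis cannot do the job the article assigns to it.

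Its size depends on assumptions the article neither makes nor excludes. With stratum effects 2 points apart and mean dropout of 30%, the bias over the rates tabulated is −0.10 to −0.68 points for w = p and +0.24 to +0.92 for w = 1/p, against +0.07 to +0.36 with no weighting. With no effect modification the cost is mainly precision. Since the analysis is optional and the primary model, alpha and sample size are untouched, severity is minor to moderate.

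**What to change.** Replace the weight definition with one sentence to this effect: each completer is weighted by the inverse of the estimated probability of completing, that is, 1/(1 − estimated probability of dropping out), from the logistic model on baseline characteristics.

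Nothing else has to change. Stabilising the weights, adding treatment arm to the dropout model and using robust standard errors for the weighted fit are reasonable refinements. They can be left to the full analysis plan, and the correction does not depend on them. The cost is one sentence, with no effect on data collection, sample size or the primary analysis.

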Cognitive Behavioural Therapy (CBT) in its current form is not suitable for persons from the non-western cultural background [10–13]. Culturally adapted Cognitive Behavioural Therapy (CaCBT) is an evidence-based practice [10, 14–18]. CaCBT is more effective than standard CBT and can reduce dropouts from therapy compared with standard CBT [19, 20]. Thus, CaCBT can increase access to mental health services and improve outcomes for immigrant, refugee and ethno-cultural and racialized populations [21–23]. Adapting CBT for growing SA populations in Canada will ensure equitable access to effective and culturally appropriate interventions. Accordingly, this study proposes to develop and evaluate CaCBT for depression and anxiety among SA populations in Canada.

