## Discussion

Research shows high rates of depression and anxiety among SA Canadians. This group also has lower rates of access to mental health care and has poorer outcomes. There are a number of psychosocial treatments available for depression and anxiety, but to the best of our knowledge, there has been no trial of any evidence-based intervention in this hard-to-reach group in Canada. As such, this is the first trial of culturally adapted CBT for South Asians in North America and Europe. This paper describes the development and testing of culturally adapted CBT. As far as we are aware, this is the first fully powered trial to compare culturally adapted CBT with standard CBT and to conduct an economic evaluation.

The impact of this intervention on service users will be to improve their mental health literacy and improve their self management capabilities through CBT. This may lead to improvement in their well-being and improve their satisfaction with health services as well as improvements in relationships, quality of life and functioning. We are undertaking a detailed process of culturally tailoring this intervention to the specific needs of our target population. This will not only help in improved efficacy but will possibly lead to fewer dropouts and higher satisfaction. The results of this study will be shared widely. Using an integrated dissemination plan, the results of the various stages will be shared through a variety of means including a launch event, webinars, manuscripts and policy reports.

The outcome of this trial will benefit health services in Canada, in terms of helping to reduce the burden of depression and anxiety and provide better care for South Asians. We expect the results to help guide the development of better services and tailor existing services to the needs of other hard-to-reach and vulnerable groups and for other cultural populations.

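### The planned LOCF analysis is not reliable evidence of robustness: it could favour whichever arm has fewer missing outcomes, and the article suggests that this may be CaCBT

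*Protocol article*

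**What the plan says.** The Statistical analyses section makes a likelihood-based mixed model, valid under missing at random (MAR), the primary analysis. Around it stand three further analyses:

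- an inverse-weighted ANCOVA in completers, which is optional and takes its weights from baseline characteristics;
- an LOCF analysis, which is a firm commitment: "a similar ANCOVA without weights will be conducted using last observation carried forward (LOCF) and all subjects";
- a per-protocol analysis, run only if non-compliance exceeds 10%.

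Of their purpose the section says: "All these extra analyses will provide information on the robustness of the primary analysis through the mixed effect model".

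On dropout, the Background says that CaCBT "can reduce dropouts from therapy compared with standard CBT", and the Discussion says that tailoring the therapy "will possibly lead to fewer dropouts and higher satisfaction". The Sample size calculation allows for substantial loss without dividing it by arm: "To account for up to 30% attrition, we plan to recruit a total of 140 participants into the study". The Measurements section sets assessments at baseline, 12 weeks and 36 weeks.

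**The concern.** LOCF treats a patient's last recorded score as the final one. With no assessment between baseline and week 12, anyone lost in that interval keeps the baseline score and counts as having gained nothing. Patients enter with a HADS subscale score of 8 or more and receive active CBT in either arm, so some fall in score is expected in both, partly through regression to the mean. The arm that loses more patients is then marked down for the loss itself, even if the two therapies work equally well.

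The article's own remarks on dropout point to standard CBT as the arm that may lose more. In that case the error in the LOCF estimate runs in the direction of the trial's hypothesis. Agreement between LOCF and the mixed model could then be read as reassurance when it partly reflects unequal follow-up. With up to 30% attrition planned for, readers are likely to look at these supporting analyses.

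**Working it through.** **Inputs from the article (Sample size calculation).** Significance level 5% (two-sided taken), power 90%, d = 0.68 or about 2.4 points, SD 3.5, 140 patients (70 per arm at 1:1), attrition up to 30%. The SD and the target are for the HADS Depression subscale.

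**Inputs not in the article, assumed here.** Mean improvement *m* of 2, 4 or 6 points in both arms; proportions missing before week 12 of 30/30%, 25/35% or 20/40% (CaCBT/standard CBT), each averaging 30%.

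**The plan's own figure.** n per arm = 2 × (1.960 + 1.282)² / 0.68² = 45.5, so 46, or 47 with the t-distribution. The article states 48, which agrees closely. 96 / 0.7 = 137.1, so 138, against 140 planned. The sample size is not in question.

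**Bias at 12 weeks, no true difference.** Let p_T and p_C be the proportions missing in the CaCBT and standard CBT arms. LOCF records a mean improvement of (1 − p_T) × m on CaCBT and (1 − p_C) × m on standard CBT. The spurious advantage for CaCBT is the difference:

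bias = m × (p_C − p_T)

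| Missing, CaCBT/CBT | m = 2 | m = 4 | m = 6 |
|---|---|---|---|
| 30/30% | 0 | 0 | 0 |
| 25/35% | 0.2 | 0.4 | 0.6 |
| 20/40% | 0.4 | 0.8 | 1.2 |

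The middle case at 20/40% is 4 × 0.20 = 0.8 points, and 0.8 / 2.4 is one third of the design difference.

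**How often the LOCF test alone would reach p < 0.05 with no true difference.** SE = 3.5 × √(2/70) = 0.59. For a bias of 0.8, 0.8/0.59 = 1.35 and the probability is 1 − Φ(1.96 − 1.35) + Φ(−1.96 − 1.35) = 27%. For 0.4 it is about 10%. A simulation of the ANCOVA (4,000 trials per case, assumed baseline–outcome correlation 0.5, dropout random within arm) gave 7%, 11% and 16% for *m* = 2, 4 and 6 at 25/35%, and 14%, 31% and 46% at 20/40%. It gave about 5% at 30/30%. An unweighted completers ANCOVA on the same data stayed at about 5% throughout, so the excess comes from carrying scores forward.

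**With a true effect δ.** LOCF estimate = (1 − p_T) × δ + m × (p_C − p_T), with *m* now the improvement on standard CBT. With equal 30% loss and δ = 2.4 this is 0.7 × 2.4 = 1.68, so LOCF shrinks the effect.

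**At week 36.** Divide the losses into early (before week 12, proportion e) and late (weeks 12 to 36, proportion l). Let *m* be the improvement to week 36 and r the worsening between weeks 12 and 36. With no true difference:

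bias = m × (e_C − e_T) − r × (l_C − l_T)

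- Half of a 20/40% loss early, scores then stable, m = 4: 4 × (0.20 − 0.10) = 0.4, half the 12-week value.
- All loss late at 20/40%, scores worsening by 1.5 points: −1.5 × 0.20 = −0.3, a bias against CaCBT.

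**The case against.** The strongest reply is that the size of the bias rests on figures the article does not contain. It gives one overall attrition ceiling, no division by arm and no expected improvement. The Background remark concerns dropout from therapy, and the Discussion remark is hedged. Patients are to be analysed as randomized whether or not they drop out, so someone who stops therapy may still be assessed. A 20/40% division (14 versus 28 of 70) would itself be conspicuous, with z about 2.6, and retention is a reported outcome. If standard CBT suits this population poorly, as the Background argues, improvement in that arm could be small and the bias with it. All of this stands: neither the direction nor the size is established.

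The scale objection also stands. The SD of 3.5 and the 2.4-point target belong to the Depression subscale, while the Statistical analyses section names the HADS total as primary. The bias formula holds on either scale, but the comparison with 2.4 points and the rejection rates apply to the subscale only.

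Three stronger readings are tempting, and the document does not support them.

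- *LOCF would falsely confirm a benefit.* It could. It could equally show no bias, dilute a real effect, or lean against CaCBT at week 36.
- *The trial's false-positive rate rises to 27% or more.* It does not. The group-by-time interaction in the mixed model decides effectiveness. A false claim that LOCF then appears to confirm needs that test to be falsely significant too; if MAR and the model hold, this happens at no more than its 5% level.
- *No analysis looks beyond MAR.* LOCF is itself a non-MAR assumption, and a graded sensitivity analysis may be in a statistical analysis plan that is not shown. Its absence from the article is not a fault.

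None of this rescues LOCF in the role the article gives it. A check whose error may be zero, positive or negative, depending on when and where patients are lost, tells the reader little by agreeing or disagreeing with the primary result.

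**Conclusion.** The point holds in limited form. The LOCF ANCOVA is a stated commitment, described as informative about robustness, and it cannot reliably fill that role here. If scores improve and more outcomes are missing before week 12 on standard CBT, it favours CaCBT by 0.2 to 0.6 points at a 25/35% division and by 0.4 to 1.2 points at 20/40%. This assumes 2 to 6 points of improvement and no true difference. The bias is smaller if many patients are lost only after week 12. The consequence is weaker supporting evidence; the primary analysis and its error rate are untouched.

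**What to change.** Replace the LOCF ANCOVA with multiple imputation carried out separately by arm, using baseline and 12-week scores, followed by a delta-adjusted tipping-point analysis. The imputation under MAR will largely repeat the mixed model; its use is as the zero-delta starting point. Then worsen the imputed scores in steps, once in the CaCBT arm alone and once in both arms, and report the delta at which the conclusion changes. The range of deltas should be prespecified and justified on the scale of the primary HADS outcome, so the plan must first settle whether that is the Depression subscale or the total.

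If LOCF is kept for comparison with older trials, remove it from the analyses said to inform robustness, and show the numbers missing by arm and visit beside it.

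The cost is a little more analysis work and, if LOCF is replaced, the loss of a familiar figure. No additional data are needed.
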